#### Severity grading and relatedness

Severity will be graded using Common Terminology Criteria for Adverse Events, Version 5.0 (CTCAE v5.0) (Grades 1–5) adapted for community settings [13]. Causality will be assigned by the study physician using WHO-UMC categories (certain, probable/likely, possible, unlikely, conditional/unclassified, unassessable) [14].

#### Clinical thresholds and actions

If ferritin rises above a pre-specified threshold (e.g., > 150 µg/L in women) and TSAT > 45%, the participant will be reviewed by the study physician; cookware use may be paused and repeat labs obtained. Any burn beyond first-degree or requiring medical care will be recorded as ≥ Grade 2 and treated/referral arranged. Initiation of therapeutic iron by outside providers will be recorded (concomitant care) and monitored for GI AEs [15, 16].

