### Exclusion criteria

Pregnant or lactating women at the time of enrolment.Women with chronic illnesses (e.g., kidney disease and inflammatory disorders) affectcting iron metabolism.Those with diagnosed or known haematological disorders (e.g., thalassemia, sickle cell anemia) based on haematological investigations such as CBC.Participants who will already using iron cookware regularly before the study.Severe dietary restrictions (e.g., vegan diets or food aversions preventing the consumption of iron-rich foods).Women who are on iron supplements or medications that interfere with iron absorption (e.g., proton pump inhibitors and certain antibiotics).Plans to relocate from the study area during the intervention period.

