### Criteria for discontinuing or modifying the intervention {15b}

Participants who become pregnant during the trial will be withdrawn from the primary outcome analysis but may be followed up for safety outcomes with consent. Data collected up to pregnancy will be retained for analysis. Participants may discontinue at their own request or if advised by the study physician for medical reasons.

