### Harms {17}

Harms included any adverse event (AE) temporally associated with trial participation/intervention, whether or not considered related, and serious adverse events (SAEs) (death, life-threatening event, inpatient hospitalization/prolongation, significant disability, or important medical events The expected AEs for this trial include minor gastrointestinal symptoms (e.g., nausea, constipation, abdominal discomfort, and dark stools); skin/contact events (e.g., minor burns while cooking); and laboratory abnormalities consistent with changes in iron status. Potential though unlikely safety signals of excess iron will be monitored using ferritin and transferrin saturation (TSAT). The participant timeline, including schedule of enrollment, interventions, and assessments, is shown in Table 2.

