#### Ascertainment and frequency

Harms will be assessed systematically at every study contact (baseline, 3, 6, and 12 months) and during monthly home visits in the intervention period, using a structured checklist and open-ended queries. Participants may also self-report harms at any time via a study phone number/WhatsApp. Field workers will document onset, duration, severity, actions taken, and outcome; supervisors verify within 48 h.

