### Allocation concealment mechanism {22}

Allocation will be concealed using sequentially numbered, opaque, sealed envelopes (SNOSE), managed exclusively by the independent statistician. Each envelope will contain the allocation code and will be opened only after eligibility confirmation and participant consent.

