### Data collection methods {25}

#### Plans for assessment and collection of outcomes {25a}

Data collection will include both quantitative and qualitative measures to evaluate iron status, dietary intake, adherence, and perceptions of the intervention. Quantitative data will be obtained through structured questionnaires to capture sociodemographic characteristics, health history, and dietary practices, as well as a 24-h dietary recall and Food Frequency Questionnaire (FFQ) to estimate dietary iron intake and food patterns. Laboratory investigations will be carried out at an NABL-accredited laboratory, where trained phlebotomists will collect blood samples for analysis of hemoglobin (Hb), serum ferritin, serum iron, soluble transferrin receptor (sTfR), transferrin saturation (TSAT), total iron binding capacity (TIBC), C-reactive protein (CRP), erythrocyte protoporphyrin, and mean corpuscular volume (MCV). These parameters will be measured at baseline, 6 months, and 12 months, with Hb and ferritin additionally assessed at 3 months. Duplicate testing will be performed on 10% of samples to ensure validity. Qualitative data will be collected through semi-structured interviews and focus group discussions (FGDs) to explore perceptions, facilitators, and barriers to cookware adoption and BCC acceptability, supplemented by field observations recorded during household visits to triangulate adherence and contextual factors. All assessors and laboratory staff will be trained and blinded to group allocation, and standard operating procedures (SOPs) will be followed at all stages to ensure consistency and data quality.

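### The iron-excess rule needs ferritin and TSAT together, but only ferritin is scheduled at the 3-month harms visit, so the rule cannot be evaluated from scheduled tests between baseline and 6 months

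*Protocol article*

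**What the plan says.** All references are to the protocol article.

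- **The rule.** Harms {17} names ferritin and TSAT as the markers for excess iron. Clinical thresholds and actions turns them into a joint trigger, "If ferritin rises above a pre-specified threshold" (150 µg/L is given as an example) together with TSAT above 45%. The consequence is that "the participant will be reviewed by the study physician; cookware use may be paused and repeat labs obtained". No visit is named.
- **The laboratory schedule.** Section {25a} lists Hb, ferritin, serum iron, sTfR, TSAT, TIBC, CRP, erythrocyte protoporphyrin and MCV, and then says: "These parameters will be measured at baseline, 6 months, and 12 months, with Hb and ferritin additionally assessed at 3 months". Table 1 also gives TSAT at baseline, 6 and 12 months only.
- **The harms schedule.** Ascertainment and frequency makes baseline, 3, 6 and 12 months harms contacts, with monthly home visits in the intervention period. Table 1 names iron overload among the adverse events and summarises them at 3, 6 and 12 months.
- **The intervention period.** Group BCC sessions and home visits run for 6 months (Health education and BCC sessions).
- **Entry and allocation.** The eligibility criteria set no ferritin or TSAT limit. The allocation envelope "will be opened only after eligibility confirmation and participant consent".

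**The concern.** A rule with two conditions can work only when both values are available. At 3 months one of them is not scheduled. A woman whose ferritin has passed the limit by then meets half of the trigger, and the stated rule requires nothing further: the repeat tests it mentions follow only after both limits have been exceeded. If her TSAT is also high, the protocol's own criterion for review is met but goes unseen until 6 months unless someone chooses to order the test.

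A smaller point concerns baseline. Both values are measured then, but no stated step compares them with the limits before cookware is handed over, and the verb in the rule suggests a change during the study.

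What is at stake is a timely clinical review for a small number of women. The between-arm comparison is not at stake.

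**Working it through.** The plan computes no figure on this point. The check sets the two schedules side by side and then sizes the result.

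**Step 1. Measurement times in months (section {25a}, TSAT confirmed in Table 1)**

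| Marker | 0 | 3 | 6 | 12 |
|---|---|---|---|---|
| Ferritin | yes | yes | yes | yes |
| TSAT | yes | no | yes | yes |
| Serum iron | yes | no | yes | yes |
| TIBC | yes | no | yes | yes |
| Harms contact | yes | yes | yes | yes |

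**Step 2. When the joint rule can be evaluated.** {0, 3, 6, 12} ∩ {0, 6, 12} = {0, 6, 12}. TSAT cannot be derived at 3 months either, because serum iron and TIBC share its schedule. The first joint check after baseline is at 6 months.

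**Step 3. Gaps between joint checks.** Now: 6 − 0 = 6 months and 12 − 6 = 6 months. With a reflex TSAT after a high 3-month ferritin: 3, 3 and 6 months. The last interval does not change.

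**Step 4. Women affected.** The documents give no frequency for both limits being exceeded. As an assumption, take 0.1% to 1% of the 101 intervention women (Sample size {19}):
- 101 × 0.001 = 0.10
- 101 × 0.01 = 1.01

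The text points to the low end. Anaemia prevalence in the two districts is 54 to 59% (Study setting {13}), iron-supplement users are excluded, and Harms {17} itself regards excess iron as unlikely.

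**Step 5. Extra TSAT tests at 3 months.** As an assumption, 1% to 5% of women have ferritin above the limit then.
- With all 202 women: 202 × 0.01 = 2.0 and 202 × 0.05 = 10.1
- With the planned 10% attrition already complete (202 × 0.9 = 181.8, about 182): 182 × 0.01 = 1.8 and 182 × 0.05 = 9.1

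Either way the number is about 2 to 10 tests.

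**The case against.** The strongest reply is that this is a condensed article, and that a two-marker rule applied at full-panel visits, with ferritin alone in between, is a coherent low-risk design. The absence of an operational step would indeed be no finding by itself. Here, however, both the rule and the laboratory schedule are stated, and they do not fit together at a visit where harms are assessed.

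A second reply is that other routes exist, and this largely stands:
- Harms {17} counts laboratory abnormalities reflecting iron status as expected adverse events.
- Under Severity grading and relatedness, the study physician assigns causality.
- Reporting and timelines sends monthly adverse-event summaries to the internal safety monitor.
- Section {28b} requires immediate reporting of unexpected safety signals, with iron overload as an example.
- Section {15b} adds that "Participants may discontinue at their own request or if advised by the study physician for medical reasons".

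A reader might infer that a high 3-month ferritin would go unnoticed until 6 months. The documents do not support that. What they lack is any step that requires the TSAT needed to apply the rule.

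A third reply concerns baseline. A reader might infer that the rule excludes baseline, so that a woman already above both limits is bound to receive cookware without review. That is too strong. The rule names no visit, its verb can simply mean exceeds, and baseline is a listed harms contact. What remains is an ambiguity that is easily removed.

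Finally, Table 2, the participant timeline, is a figure that could not be read for this check. If it schedules TSAT at 3 months, the 3-month point falls and section {25a} should be brought into line with it.

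**Conclusion.** The point holds as a minor participant-safety misalignment, worth correcting because correction is cheap. From scheduled tests, the joint rule cannot be evaluated between baseline and 6 months, although 3 months is a harms visit. Under the assumed range of 0.1% to 1%, about 0.1 to 1.0 of the 101 intervention women would be affected. That range is an assumption, since the documents give no prevalence. The schedule rests on section {25a} and Table 1.

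Three stronger readings should not be drawn:
- It is not a contradiction. Each statement can be followed as written.
- It does not bias any comparison or affect power.
- It does not show that eligibility needs a ferritin or TSAT limit, or that allocation must wait for laboratory results.

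**What to change.** 1. **Reflex test at 3 months.** When 3-month ferritin is above the limit, run TSAT (serum iron and TIBC), on the same sample where possible, and apply the existing rule. The laboratory works on coded samples, so a reflex triggered by the ferritin value treats both arms alike and reveals no allocation.
2. **Wording of the rule.** State that it applies when ferritin *is above the limit and TSAT > 45% at any measurement, including baseline*. The clinical investigators keep the choice of limit and action.
3. **Baseline check.** Compare baseline ferritin and TSAT with the limits before cookware is issued, in the same way in both arms. Holding the allocation envelope until the results are back is an option but not part of this fix.

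**Cost.** About 2 to 10 extra TSAT assays at 3 months under the stated assumption, no new baseline assay, and possibly a short delay before cookware is issued. The interval from 6 to 12 months stays as it is, so a rise soon after month 6 would still wait for the 12-month panel.

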### Reporting and timelines

Serious adverse events (SAEs): notified to the Principal Investigator and ethics committee within 24 h; reported to the sponsor and registry per local regulations.Adverse events (AEs): summarized and reported monthly to the internal safety monitor and quarterly to the ethics committee.Unanticipated problems posing risk to participants or community will be reported promptly and corrective actions documented.

#### Data safety oversight

An independent safety monitor/DSMB (if required by IEC) will review blinded AE/SAE listings after ~ 25% and ~ 50% of expected person-time. The DSMB/sponsor may recommend protocol modifications, temporary suspensions, or terminations for safety concerns.

#### Medical management and compensation

Participants with AEs receive appropriate first aid, referral, and follow-up at no cost as per institutional policy and national regulations. Compensation for research-related injury will follow institutional ethics guidelines.

#### Documentation

All harms will be recorded in source notes and the eCRF, with MedDRA coding (if applicable), and included in interim/final reports and trial publications.

### Participant timeline {18}

#### Sample size {19}

The sample size was calculated based on hemoglobin (Hb) as the key outcome variable. Considering a standard deviation (SD) of 1.2 g/dL and a minimum detectable difference (Δ) of 0.5 g/dL between the intervention and control groups, the required sample size was estimated to provide 80% power (*β* = 0.20) at a two-sided significance level of 5% (*α* = 0.05, 95% confidence level). The sample size was adjusted accordingly to account for an anticipated 10% attrition due to loss to follow-up, pregnancy, or withdrawal. The final required sample size is 202 participants, with 101 participants allocated to the intervention group and 101 participants to the control group [18, 19]. Since we will pool the data from two sites for the main outcome measures, the total sample size will be equally divided into two study sites.

The sampling strategy for this study involves a multi-stage approach to ensure methodological rigor and reduce potential biases. Initially, eligible villages will be purposefully selected from study areas based on predefined inclusion criteria such as population size, accessibility, and anemia prevalence data, if available. Within each selected village, a household listing will be conducted to identify households with at least one eligible non-pregnant, non-lactating (NPNL) woman of reproductive age. In instances where more than one eligible woman resides in a single household, one participant will be selected using simple random selection methods—such as a coin toss or random number generation—to prevent intra-household clustering and to maintain the independence of observations. This ensures that each household contributes only one participant to the study. Following this, the identified households will be subjected to block randomization, as previously described, to assign participants into intervention and control groups in balanced proportions. This sampling framework enables equitable group allocation, reduces selection bias, and ensures that the study sample is representative of the target population within the selected geographic context.

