### Outcomes {16}

The outcome measures and assessment time points are summarized in Table 1. Blood samples will be collected at each time point for the biochemical analysis of iron status markers. Dietary intake and adherence to cookware use will be monitored using structured questionnaires and periodic household visits.

**Table 1 Tab1:** Summary of primary, secondary, and exploratory outcomes with measurement variables, analysis metrics, aggregation methods, and time points (baseline to 12 months)

Outcome type	Measurement variable	Analysis metric	Method of aggregation	Time points
Primary outcome	Serum ferritin (µg/L), CRP-adjusted	Mean change from baseline	Mean ± SD, mean difference (95% CI)	Baseline, 6 months, 12 months
Secondary outcomes	Haemoglobin (g/dL)	Mean change from baseline	Mean difference (95% CI)	Baseline, 6 months, 12 months
	Soluble transferrin receptor (mg/L)	Mean change from baseline	Mean difference (95% CI)	Baseline, 6 months, 12 months
	Transferrin saturation (%)	Mean change from baseline	Mean difference (95% CI)	Baseline, 6 months, 12 months
	Anaemia prevalence (Hb < 12 g/dL, WHO)	Proportion with anaemia	Risk difference, risk ratio (95% CI)	Baseline, 6 months, 12 months
	Nutrition knowledge and practice score	Change in score	Mean difference	Baseline, 6 months, 12 months
	Adherence to iron cookware use (≥ 1 main meal/day, ≥ 4 days/week)	Proportion adherent	Percentage adherence	Monthly monitoring; summarised at 6 months, 12 months
	Adverse events (GI symptoms, iron overload, other harms)	Proportion with ≥ 1 adverse event	Frequency counts, percentages	Ongoing; summarised at 3, 6, and 12 months
Exploratory outcomes	Cost-effectiveness (per unit Hb and ferritin increase)	Incremental cost-effectiveness ratio (ICER)	ICER	6 months, 12 months
	Dietary modifiers (vitamin C intake, tea/coffee, phytates)	Effect modification	Subgroup analyses	Baseline, 6 months, 12 months
	Subgroup analysis by baseline anaemia	Effect difference	Interaction tests	6 months, 12 months
	Community-level adoption of cookware post-trial	Proportion of households continuing usage	Adoption rate (%)	Endline at 12 months; post-trial sustainability follow-up

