### Statistical methods {27}

#### Primary and secondary outcomes {27a}

Descriptive statistics will be used to summarize baseline characteristics. Continuous variables will be expressed as mean (SD) or median (IQR) as appropriate, and categorical variables as frequencies and percentages. Baseline differences between intervention and control groups will be assessed using independent *t*-tests (or Mann–Whitney *U* tests for non-normal data) and chi-square or Fisher’s exact tests for categorical variables. Standardized mean differences (SMDs) will be calculated, with an SMD < 0.1 indicating adequate baseline balance.

Continuous outcomes such as haemoglobin (Hb), serum ferritin, soluble transferrin receptor (sTfR), and transferrin saturation (TSAT) will be analyzed using linear mixed-effects models with fixed effects for group, time, and group × time interaction, and random effects for participants (and clusters if applicable). Binary outcomes such as anaemia prevalence, adherence, and adverse events will be analyzed using mixed-effects logistic regression. Risk ratios, odds ratios, mean differences, and 95% confidence intervals will be reported. The significance level will be set at *p* < 0.05 (two-tailed). Analyses will be performed using R software.

To provide a comprehensive evaluation of iron status, additional biomarkers will be assessed, including total iron-binding capacity (TIBC), erythrocyte protoporphyrin, mean corpuscular volume (MCV), and C-reactive protein (CRP). These indicators will enable differentiation between iron deficiency, anaemia of inflammation, and other causes of low Hb. Effect size (Cohen’s d) will be calculated for the primary outcomes (Hb and ferritin) to quantify the magnitude of intervention impact**.**

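### The protocol gives three conflicting outcome hierarchies, and its 80% power and 202 women apply only to haemoglobin, so ferritin, primary in two of the three, has no stated power

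*Protocol article*

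**What the plan says.** Three places in the protocol article bear on this.

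- **Outcomes {16}, Table 1.** The only row labelled as primary is "Serum ferritin (µg/L), CRP-adjusted", with mean change from baseline as the metric. The first row of the secondary block is "Haemoglobin (g/dL)".
- **Sample size {19}.** "The sample size was calculated based on hemoglobin (Hb) as the key outcome variable". The target effect is "a minimum detectable difference (Δ) of 0.5 g/dL between the intervention and control groups". The planning SD for Hb is 1.2 g/dL, and the aim is 80% power in a two-sided 5% test. After 10% attrition the total is 202, or 101 per arm.
- **Primary and secondary outcomes {27a}.** "Effect size (Cohen’s d) will be calculated for the primary outcomes (Hb and ferritin)". Here both markers are called primary.

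No section gives an SD, a target difference, a sample size or a power for ferritin.

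**The concern.** The primary outcome decides what counts as success, and the planning power is meant to describe the trial's ability to answer that question. Here the two are not tied together. Under Table 1, the 80% describes a secondary outcome. Under section 27a, it describes one of two primaries. Only if Hb alone is primary does it describe the primary outcome, and no section says that outright.

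Two things are at stake. First, with the hierarchy open, whichever marker reaches significance could be presented as the primary result. Second, a non-significant ferritin result could be read against an 80% power figure that was never worked out for ferritin.

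**Working it through.** **Step 1. Reproduce the plan's figure.** Inputs from Sample size {19}: SD 1.2 g/dL, difference 0.5 g/dL, two-sided alpha 0.05, power 80%, attrition 10%. Trial design {12} gives 1:1 allocation.

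n per arm = 2 × (1.960 + 0.8416)² × 1.2² / 0.5² = 90.4

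Inflated for attrition: 90.4 / 0.9 = 100.5, so 101 per arm and 202 in total. This matches. (Rounding up to 91 first gives 91 × 1.1 = 100.1, again 101; 91 / 0.9 gives 102, or 204 in total. The difference is trivial.) The stated size therefore comes wholly from Hb, and the arithmetic is right for Hb.

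**Step 2. Set the hierarchies side by side.**

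| Place | Hb | Ferritin | What the 80% covers |
|---|---|---|---|
| Table 1 | secondary | sole primary | a secondary outcome |
| Sample size {19} | key outcome | not mentioned | the key outcome |
| Section 27a | primary | primary | one of two primaries |

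These cannot all hold, and no other section reconciles them.

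**Step 3. What the size implies for any outcome.** Evaluable per arm: 101 × 0.9 = 90.9, about 91. Without baseline adjustment, the standardised difference detectable at 80% power is

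2.80 × √(2/91) = 0.415 SD of the analysed quantity.

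The Hb target is 0.5 / 1.2 = 0.417 SD, which is why Hb reaches 80%. The figure carries over to ferritin only if ferritin's true standardised effect is also about 0.42, and the document gives nothing from which to judge that. For assumed effects of 0.20, 0.30, 0.40 and 0.50 SD, the power at 91 per arm is 27%, 53%, 77% and 92% (normal approximation).

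**Step 4. Illustration for ferritin (all inputs assumed).** The document gives no ferritin SD, target or baseline correlation. I assume an SD of ln(ferritin) of 0.7 to 1.0, a true ratio of geometric means of 1.3, and 91 per arm, using a two-sample t-test. The standardised effect is ln(1.3) / SD = 0.262 / SD.

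- Follow-up value only: power 71% (SD 0.7) to 42% (SD 1.0). Detectable ratio exp(0.415 × 0.7) = 1.34 to exp(0.415 × 1.0) = 1.51.
- Change from baseline, assumed correlation 0.7: the SD is multiplied by √(2 × (1 − 0.7)) = 0.775. Power 90% to 62%; detectable ratio 1.25 to 1.38.
- Baseline-adjusted, same correlation: the SD is multiplied by √(1 − 0.7²) = 0.714. Power 94% to 69%; detectable ratio 1.23 to 1.35.

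The log scale is mine. Table 1 gives ferritin in µg/L as a mean change and does not mention logs. On the µg/L scale, if the SD of the change were 10, 20 or 40 µg/L (assumed), the detectable difference would be 0.415 × SD, or 4.2, 8.3 or 16.6 µg/L.

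**The case against.** The strongest reply is that Hb may be the intended primary outcome. The sample size section calls it the key variable, and the abstract and the first objective name it before ferritin. On that reading the calculation is correct and Table 1 is the error. This stands as far as it goes: the document does not show which version was meant, and ferritin should not be assumed to be the answer. But the contradiction remains, and ferritin is primary in Table 1 and in section 27a alike.

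A second reply is that joint primaries make powering on Hb acceptable. Table 1 does not say they are joint, and section 27a gives ferritin no power either. If success on either marker were enough and alpha were split to 0.025 each, Hb alone would need 110 per arm before attrition: 110 / 0.9 = 122.2, so 123 per arm and 246 in total.

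A third reply is that the analysis plan will settle it. That plan may exist, but the article states the primary outcome and the sample size basis itself, and those published statements conflict with each other.

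A reader might infer from all this that the trial is underpowered for ferritin. The documents do not support that. No ferritin power can be computed from them, and the follow-up-only figures above ignore baseline, whereas Table 1 plans change from baseline, section 27a a longitudinal model, and Additional analyses {27d} lists baseline iron status among the covariates. If the baseline correlation is high, power rises materially, as Step 4 shows.

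**Conclusion.** The point holds as a contradiction about which outcome is primary, with a direct consequence for the power statement. The 202 women and 80% power are correct for Hb at 0.417 SD and apply to Hb only. Ferritin, which is primary under two of the three versions, has no stated power.

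This conclusion rests on the document's own text and on arithmetic that reproduces its own figure; it needs no outside assumption. The ferritin powers in Step 4 are different. They depend on an assumed SD, true ratio, scale and correlation, and run from 42% to 94% for a ratio of 1.3. They show that the 80% cannot simply be transferred to ferritin, in either direction. They do not show that 202 is too few, nor that it is enough.

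This should be corrected before recruitment, which Trial status puts at December 2025.

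**What to change.** Choose one hierarchy and make Table 1, Sample size {19} and section 27a agree, together with the registration if it differs (the registry record was not available for this review). Either option is sound.

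- **Option (a): ferritin is the single primary.** Label the 0.5 g/dL, 80% statement as applying to the secondary outcome Hb. Add to Sample size {19} the ferritin effect detectable with 202 randomised and 10% attrition: about 0.42 SD of the analysed quantity without baseline adjustment. Give the SD, the scale and the baseline correlation assumed, on the same scale as the primary analysis. In section 27a, refer to ferritin as the primary outcome and Hb as secondary.
- **Option (b): Hb is the primary.** Change Table 1 and section 27a so that Hb is primary and ferritin secondary. The existing calculation then stands.

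The cost is an amendment through the route in Protocol amendments {31}, plus one calculation under (a). The drawback of (a) is that the stated power for the primary outcome may look less favourable. Whether 202 remains the right number under (a) can be judged only once a ferritin target and SD are written down.
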